### Participants

This study proposes the following inclusion criteria: (1) infants who are clinically stable in a NICU, born at a minimum of 28 weeks and less than 32 weeks GA; (2) birth weight between the 10th and 90th percentiles of the average birth weight for the same GA, identified as appropriate [2]; and (3) parents agreeing to participate in the study and for follow-up diagnosis and treatment at the designated hospital for one year after discharge. The exclusion criteria will include the following: (1) congenital malformation in the infant that interferes with the intervention or for which the intervention interferes with the required care (e.g., complex congenital heart disease, complex gastrointestinal malformations, diaphragmatic hernia); (2) severe nervous system malformations or disorders (e.g., bilirubin encephalopathy, central nervous system infection, intracranial hemorrhage of ≥degree III); (3) independent predictors of disturbed sleep or neurodevelopment (e.g., inborn metabolism errors, preeclampsia, bronchopulmonary dysplasia); and (4) visual or hearing impairment. Those with the following criteria would be exited from the study: (1) terminating treatment or death during the study period or (2) adverse clinical events likely associated with receiving the multisensory stimulation bundles, or severe adverse events possibly related to the multisensory stimulation bundles.

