#### Secondary outcomes

Secondary study outcomes will include the following variables:Other sleep indicators: Sleep duration, fragmentation index, and amplitude of limb movement will also be obtained using the actigraphy watch (model: Actiwatch-2).Burdjalov Score: The Burdjalov Score is a scoring system used to evaluate the brain maturation of neonates. It is measured through aEEG examinations (CFM3000). It comprises four component variables: (1) presence or absence of “sleep–wake cycling,” (2) continuity of the brainwave record pattern, (3) recording bandwidth, and (4) lower-border amplitude (in μV) (see Table 1). Each variable will be independently evaluated, and each participant’s scores will be summed to determine the total score for each recording [33]. The minimum and maximum possible total scores are 0 and 13, respectively. A qualified physician will conduct bedside aEEG examinations, which involve continuous data collection over 4 h at baseline, week 2, and week 4 after randomization (see Fig. 2). Afterward, the physician will interpret the aEEG data to calculate the Burdjalov Score. During the aEEG examination, the room temperature will be maintained at 24–28°C, while unnecessary iatrogenic procedures on the infant will be minimized.The Griffiths Mental Development Scales (GMDS) with six subtests will be used to assess neurodevelopment in children aged 0–2 years [34, 35]. Each subtest measures a different development area: (A) locomotor, (B) personal–social, (C) hearing and language, (D) eye and hand coordination, (E) performance, and (F) practical reasoning. The mental age (MA) is derived by calculating the average raw scores of the six subtests. The corrected age (CA) is calculated as the difference between the examination and birth dates. The developmental quotient (DQ) is expressed as a mental ratio, i.e., DQ = (MA / CA) × 100. Finally, the total development quotient is represented by GQ, which represents the average value of all the development quotients [35]. The scale is culturally appropriate for Chinese children [35]. In this study, two physician research assistants with international GMDS qualifications will conduct GMDS assessments on study participants. Furthermore, the assessment process will be video-recorded for possible replay. Interrater measurement consistency will be obtained prior to the actual assessment of infants to reduce errors.Growth indicators at follow-up will include weight, length, and head circumference. Moreover, the research assistant will collect data when participants return for follow-up at 3, 6, and 12 months of CA.

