### Data analysis

The baseline characteristics of the samples will be presented as *N* (%) for categorical variables and mean ± SD or median (IQR) for quantitative variables, depending on the data distribution. The primary and secondary outcomes will be analyzed using a linear mixed-effect model with “intervention” as a between-subjects factor and “time” as a within-subjects factor. The primary outcome (sleep efficiency) will be evaluated at timing points of week 2 (T2 timing point) and week 4 (T4 timing point) after randomization during the hospitalization. We compared the mean difference between primary and secondary outcomes as follows: group A (T2) vs. group B (T4) and group A (T4) vs. group B (T2). Moreover, every participant will receive the investigated intervention, and the difference between the groups will be the order in which they receive it. Therefore, no statistical difference would exist between groups during the follow-up period. Hence, we will only conduct the statistical description of the follow-up indicators. No statistical test will be prespecified regarding the follow-up indicators in this study. The intention-to-treat analysis will be used for missing values during each data collection. Although cases of missing data are expected to be rare, multiple imputations assuming random missing data will be used for this study. SPSS software version 24.0 (IBM Corp., Armonk, NY, USA) will be used for data analysis. Two-tailed *p*-values < 0.05 will be considered indicative of statistical significance.

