## Abbreviations

aEEG: Amplitude-integrated electroencephalography
AE: Adverse event
AS: Active sleep
ASE: Active sleep efficiency
CA: Corrected age
CRF: Case report form
CTCAE: Common Terminology Criteria for Adverse Events
DQ: Developmental quotient
GA: Gestational age
GMDS: Griffiths Mental Development Scales
IS: Indeterminate sleep
MA: Mental age
NICU: Neonatal intensive care units
PI: Principal investigator
QS: Quiet sleep
REM: Rapid eye movement
SOP: Standard operating procedure
TST: Total sleep time efficiency
VPI: Very preterm infants

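### Corrected age is defined as examination date minus birth date, which is chronological age; applied as written, it makes every Griffiths quotient too low, most of all in the most preterm infants

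*Protocol article*

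**What the plan says.** The Griffiths paragraph of the protocol article (Secondary outcomes) gives an explicit rule for age: "The corrected age (CA) is calculated as the difference between the examination and birth dates". It then uses that age as a denominator: "The developmental quotient (DQ) is expressed as a mental ratio, i.e., DQ = (MA / CA) × 100". The total score carries the same denominator, since "the total development quotient is represented by GQ, which represents the average value of all the development quotients". Follow-up is set in the same unit: "participants return for follow-up at 3, 6, and 12 months of CA".

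The abbreviation list confirms the intended meaning, "CA: Corrected age", so CA was not meant as chronological age. The Participants section restricts entry to infants "born at a minimum of 28 weeks and less than 32 weeks GA". For the follow-up period, Data analysis says: "Hence, we will only conduct the statistical description of the follow-up indicators". Nowhere does the article subtract the weeks of prematurity.

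**The concern.** The label and the formula describe two different quantities. Examination date minus birth date is age since birth. Corrected age is that figure less the time by which the infant was born early. In a term population the two would nearly coincide. Here every participant is born at least eight weeks before 40 weeks, so they differ in every infant.

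Three things are at stake if the sentence is followed:

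- **Level.** Quotients come out too low in infants who are developing normally for corrected age. Because the follow-up is only described, these levels are the result, and there is no planned contrast between sequences in which a shared error would cancel.
- **Gradient.** The error grows with prematurity, so it puts an artificial dependence on gestational age into the quotient. The second objective is to observe how sleep in hospital relates to first-year neurodevelopment, and the Introduction says that sleep changes in preterm infants depend heavily on gestational age. An artefact tied to gestational age could therefore create or inflate an apparent link between sleep and development.
- **Timing.** If visits are booked with the same formula, they fall at the wrong developmental age.

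**Working it through.** The article gives no figure for the quotient to reproduce; the check is on a definition.

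**Inputs**

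- Gestational age (GA) at birth: 28+0 to 31+6 weeks (Participants).
- Visit ages: 3, 6 and 12 months of CA (Secondary outcomes).
- DQ = 100 × MA / CA, where MA is mental age (Secondary outcomes).
- Assumption: term is 40 weeks. The article states no reference, so 37 weeks, the preterm threshold given in its Introduction, is run as a lower bound.
- One month = 365.25 / 12 / 7 = 4.348 weeks.

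**Step 1: gap between the stated age and corrected age**

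Gap = (term − GA) / 4.348 months. With term at 40 weeks:

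- GA 28+0: 12 / 4.348 = 2.76 months
- GA 31+6: 8.14 / 4.348 = 1.87 months

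**Step 2: visits held at true corrected age, quotient computed with the stated formula**

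Take an infant exactly on target, so that MA equals true corrected age and the true DQ is 100. The stated formula gives

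DQ = 100 × corrected age / (corrected age + gap).

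For example, at 3 months and GA 28+0: 100 × 3 / (3 + 2.76) = 52.1.

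| Term reference | GA at birth | 3 months | 6 months | 12 months |
|---|---|---|---|---|
| 40 weeks | 28+0 | 52.1 | 68.5 | 81.3 |
| 40 weeks | 31+6 | 61.6 | 76.2 | 86.5 |
| 37 weeks | 28+0 | 59.2 | 74.4 | 85.3 |
| 37 weeks | 31+6 | 71.7 | 83.5 | 91.0 |

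With term at 40 weeks, the shortfall from 100 is about 38–48, 24–32 and 14–19 points at the three ages. The artificial difference between the two ends of the GA range is 61.6 − 52.1 = 9.5 points at 3 months and 86.5 − 81.3 = 5.2 points at 12 months.

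**Step 3: a separate scenario, visits also booked with the stated formula**

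With term at 40 weeks, a visit booked at 3 months since birth falls at 3 − 2.76 = 0.24 to 3 − 1.87 = 1.13 months of true corrected age. The on-target infant's quotient is then 100 × (visit age − gap) / visit age:

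| GA at birth | 3 months | 6 months | 12 months |
|---|---|---|---|
| 28+0 | 8.0 | 54.0 | 77.0 |
| 31+6 | 37.6 | 68.8 | 84.4 |

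Steps 2 and 3 are alternatives; both cannot apply to the same visit.

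**Step 4: after correction**

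If the gap is subtracted from the denominator and the visit is held at true corrected age, the on-target infant scores 100 at every GA and every visit.

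**The case against.** The strongest reply is that this is a drafting slip. The quantity is named corrected age, the abbreviation list says the same, visits are set in that unit, and the assessors hold international Griffiths qualifications. On that view staff would subtract prematurity whatever the sentence says, and nothing in the article shows that any quotient has been derived wrongly. This is fair, and it makes the harm conditional on the formula being applied. It does not rescue the text: the article gives an operational formula, and that formula is wrong for its own term. This also goes beyond detail that an article leaves to a fuller document.

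Second, the consequences for the trial are limited. The quotient is secondary, follow-up is descriptive, both sequences share the error, and the primary endpoint, sample size and primary model are untouched. All of that stands. The quotient levels and their spread by gestational age are nonetheless what will be published.

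Third, the largest figures assume that the Griffiths scales are given at 3 months. The sentence naming 3, 6 and 12 months follows the one on growth indicators, and the schedule figure is not available here. Griffiths testing at all three visits is a reasonable inference but remains an inference. If only the 12-month assessment counts, the shortfall is 14–19 points with a 40-week reference and 9–15 with 37 weeks.

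Fourth, the error is recoverable at analysis, because gestational age and the dates are available. That holds for the quotient, but not for visits that were actually booked at the wrong age.

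**Conclusion.** The definition is wrong as written. It calls chronological age corrected age and makes it the denominator of every Griffiths quotient in a cohort born entirely before 32 weeks. If it is followed, quotients are too low in every scenario examined and lowest at the lowest gestational age. With visits at true corrected age and term at 40 weeks, an infant with a true DQ of 100 would be reported at 52–62, 69–76 and 81–87 at 3, 6 and 12 months. The result rests on three things: the formula being applied literally, the term reference (a 37-week reference reduces the error but does not remove it), and the inferred Griffiths schedule for the 3- and 6-month figures. The primary comparison is not affected. The definition should be corrected before any follow-up quotient is reported.

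**What to change.** Replace the sentence with: corrected age = (examination date − birth date) − (term reference − gestational age at birth), all in the same time unit. State the term reference explicitly, for example 40 weeks. Use this one definition both in the DQ denominator and for the 3-, 6- and 12-month visit windows.

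Recruitment began in April 2022, so some follow-up assessments may already have taken place. Check which age was used to derive any existing quotients and to book visits. Recompute any quotient derived with the stated formula. If any visit was booked by age since birth, report the true corrected age at that assessment.

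The cost is a one-line text change and, if needed, a recalculation. Gestational age is already collected (Control variables and covariates), and the two dates are already in the formula, so no new data are required.

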### Adverse events (AEs)

In this study, AEs will refer to all adverse medical events that occur during the study period, which may be manifested by signs, symptoms, disease, or abnormal laboratory tests. According to Common Terminology Criteria for Adverse Events (CTCAE), AEs in this study include impaired skin integrity, skin allergies, fever, and fluctuating oxygen saturation, even the disease deterioration requiring surgery, cardiopulmonary resuscitation, and ventilator parameter model upgrade, among others. The CTCAE, a grading scale helps to determine and assess the severity of a clinically adverse event, which displays grades 1 through 5 (indicating mild, moderate, severe, life-threatening consequences, and death) [36]. Meanwhile, WHO-UMC (UMC, Uppsala Monitoring Center) displays the association of AEs with experimental interventions (indicating certain, likely, possible, unlikely, conditional/unclassified, nonassessable/unclassifiable) [37]. The study will be terminated, when any AEs that are likely or certain to be associated with intervention or severe AEs that are possibly, likely, or certain related to the intervention. The AEs will be recorded in a case report form (CRF) within 24 h of occurrence. Severe AEs will be immediately reported to the Hospital Research Ethics Committee, followed by suspension of the study. The AE occurrence ratio will be calculated and analyzed.

### Control variables and covariates

To characterize the sample and ensure balance across groups in analyses for treatment effects, we will prospectively collect the following information from electronic medical records and parent report questionnaires to control for the following: (1) major medical complications associated with prematurity, including GA, birth weight, sex, history of antenatal steroid usage, infection, number of days of intubation and oxygen, and X-ray changes consistent with chronic lung disease; (2) postmenstrual age at sleep and aEEG measurement; and (3) the number of days of exposure to study treatment. We will also obtain metrics to ensure balance across groups. If the groups do not match, we will use the unmatched metric as a covariate in the analyses.

### Data collection

All data collection collaborators will receive detailed training on the study process before starting the study to ensure the homogeneity and integrity of data collection. During the hospital stay, outcome measurements will be conducted by reviewing medical records, including medical notes and nursing care charts, as well as using the Actiwatch-2 Actigraph, aEEG, and GMDS for data collection. Further, The data collectors must have obtained the necessary licenses, such as aEEG and GMDS qualifications. Data collected after withdrawal of participation and the participants’ hospital mortality would be the only reasons for the non-inclusion of data. All forms completed by the outcome measurement, screening, and enrollment teams will be entered into an electronic platform; and two staff members will work together on data entry to minimize input mistakes. The Epi Data software will be used to control the range and accuracy of the data entered. The schedule for outcome assessments is shown in Fig. 2.

### Data quality and monitoring

For this study, an eCRF record must be completed for each patient. Data will be anonymized by assigning a unique code for each participant. The critical document containing each patient’s name related to the code number will be stored in the folder of the principal investigator (PI) at each center. Data will be kept in an institutional research location of the PI, secured with a password or key for the period specified by legislation. The SCMC Clinical Research Department will engage relevant experts to form an independent data monitoring committee (IDMC). The IDMC will conduct periodic monitoring visits during the trial, which will include data collection, patient safety, and research progress.

### Sample size calculation

In the previous pilot study conducted during October 2021 to February 2022, five participants in the intervention group vs five with matched characteristics in the control group were compared. The primary outcome (defined as sleep efficiency) was found to be 0.52 and 0.48 in the intervention and control group, respectively. The intervention effect size was estimated to be 0.04, and the inter-person standard deviation, 0.05. Considering a two-tailed significance level of 5% (α) and a test power of 90%, the required sample size is 36, with 18 in each group. Considering a dropout rate of 10%, 40 participants will be recruited for this study. In the past 5 years, the study setting received more than 100 VPIs every year, which means the sample size could be achieved in the planned time frame.

### Data analysis

The baseline characteristics of the samples will be presented as *N* (%) for categorical variables and mean ± SD or median (IQR) for quantitative variables, depending on the data distribution. The primary and secondary outcomes will be analyzed using a linear mixed-effect model with “intervention” as a between-subjects factor and “time” as a within-subjects factor. The primary outcome (sleep efficiency) will be evaluated at timing points of week 2 (T2 timing point) and week 4 (T4 timing point) after randomization during the hospitalization. We compared the mean difference between primary and secondary outcomes as follows: group A (T2) vs. group B (T4) and group A (T4) vs. group B (T2). Moreover, every participant will receive the investigated intervention, and the difference between the groups will be the order in which they receive it. Therefore, no statistical difference would exist between groups during the follow-up period. Hence, we will only conduct the statistical description of the follow-up indicators. No statistical test will be prespecified regarding the follow-up indicators in this study. The intention-to-treat analysis will be used for missing values during each data collection. Although cases of missing data are expected to be rare, multiple imputations assuming random missing data will be used for this study. SPSS software version 24.0 (IBM Corp., Armonk, NY, USA) will be used for data analysis. Two-tailed *p*-values < 0.05 will be considered indicative of statistical significance.

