### Interventions with participants and investigation equipment

Participants will receive two types of care—“standard care” and “standard care plus multisensory stimulation bundles”—randomly for two consecutive weeks each (see schedule of enrollment, interventions, and assessments in Fig. 2). Thus, every participant will receive the tested intervention. The difference between the groups will only be the order in which they receive the intervention. Furthermore, all healthcare providers will receive detailed training on the study process before the study commences. To ensure precise and standard sensory stimulations, we will provide the multisensory stimulation bundles using the multisensory stimulation-supported device. The device application’s standard operating procedure (SOP) has been developed. All healthcare providers involved in VPI care will be trained to apply the device and standard care through presentations and bedside demonstrations prior to the start of the study, ensuring intervention homogeneity.

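### Intervention is specified as a between-subjects factor and the two listed contrasts compare like with like, so no stated main effect or contrast estimates intervention versus standard care; the sample size rests on a within-infant analysis that the text does not describe

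*Protocol article*

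**What the plan says.** **Design.** The protocol article, Interventions with participants and investigation equipment, describes two weeks of each type of care in random order: "Thus, every participant will receive the tested intervention". It adds that only the order differs between groups A and B, and the Data analysis section repeats this.

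**Model.** Data analysis plans a "linear mixed-effect model with “intervention” as a between-subjects factor", with time as the within-subjects factor, for primary and secondary outcomes. Sleep efficiency is evaluated at week 2 (T2) and week 4 (T4). Two comparisons are written out: A(T2) with B(T4), and A(T4) with B(T2). No sequence term, group-by-time interaction or within-infant treatment contrast is named.

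**Sample size.** Sample size calculation states: "The intervention effect size was estimated to be 0.04, and the inter-person standard deviation, 0.05". The source is a pilot in which "five participants in the intervention group vs five with matched characteristics in the control group were compared". The result, at two-sided 5%, is "a test power of 90%, the required sample size is 36, with 18 in each group", raised to 40 for 10% dropout.

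**The concern.** In a two-period, two-sequence crossover the type of care changes within each infant. The only randomised factor that stays constant within an infant is the order, that is, group A or B. A model that treats intervention as between-subjects therefore either tests order under the wrong name or describes a different design. The two written-out comparisons do not rescue it, because neither sets intervention against standard care.

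The primary test is at stake. An analyst who follows the text literally reports a null result whatever the device does, or reports a maturation effect as if it bore on treatment. An analyst who departs from the text chooses the primary test outside the published plan. The stated power also belongs to an analysis that the text does not describe.

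**Working it through.** **1. What the stated terms estimate.** Let τ be the treatment effect and π1, π2 the period effects at T2 and T4, with no carryover. Suppose group A starts with the intervention; reversing this changes signs only. The expected values, apart from a common mean, are:

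| | T2 | T4 |
|---|---|---|
| Group A | τ + π1 | π2 |
| Group B | π1 | τ + π2 |

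- Group main effect: (A(T2) + A(T4))/2 − (B(T2) + B(T4))/2 = (τ + π1 + π2)/2 − (τ + π1 + π2)/2 = 0.
- Time main effect: the average over groups is π1 + τ/2 at T2 and π2 + τ/2 at T4, so the difference is π1 − π2.
- First listed contrast: A(T2) − B(T4) = (τ + π1) − (τ + π2) = π1 − π2.
- Second listed contrast: A(T4) − B(T2) = π2 − π1.
- Group-by-time interaction: (A(T2) − A(T4)) − (B(T2) − B(T4)) = 2τ.

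The sum of the two listed contrasts is the group effect (times 2) and their difference is the time effect (times 2). No combination of them contains τ; only the unnamed interaction does.

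**2. Size.** Simulation used τ = 0.04, SD 0.05, 18 infants per group, an assumed within-infant correlation of 0.3, and no period or carryover effect. Rejection at two-sided 5%:

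- Group main effect: 4.4% (5,000 runs) and 5.1% (20,000 runs).
- A(T2) vs B(T4): 4.1% and 4.7%.
- A(T4) vs B(T2): 4.8% (20,000 runs).

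All are at the nominal level, as the algebra requires.

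**3. Reproducing the stated 36.** Inputs from Sample size calculation: difference 0.04, SD 0.05, two-sided 5%, power 90%. For a 2×2 crossover with N infants in total and 0.05 as the within-infant SD:

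- SE = 0.05 × √(2/N), with N − 2 degrees of freedom.
- At N = 36: SE = 0.05 × √(2/36) = 0.01179, noncentrality 0.04/0.01179 = 3.39, power 90.9%.
- N = 34 gives 89.2% and N = 35 gives 90.1%, so 36 is the smallest even number that reaches 90%.
- The implied SD of the paired difference is 0.05 × √2 = 0.071.
- Dropout: 36/0.9 = 40, as stated.

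**4. Readings that do not give 36.**

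- Different infants in a single period, 18 vs 18: SE = 0.05 × √(2/18) = 0.01667, noncentrality 0.04/0.01667 = 2.40, power 64.5%. With 20 vs 20 it is 69.3%. Reaching 90% takes 34 per group, 68 in total.
- 0.05 as the SD of the paired difference: 19 infants would be enough.

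**5. If 0.05 is the total SD.** The SD of the paired difference is 0.05 × √(2(1 − ρ)), where ρ is the correlation between an infant's two measurements. The document gives no ρ. With 36 infants, power is 90.9% at ρ = 0, 97.6% at ρ = 0.3 and 99.7% at ρ = 0.5.

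**The case against.** The strongest reply is that this is loose wording in a condensed article. A model with one between and one within factor commonly carries their interaction, and here that interaction is the treatment effect: with 18 infants per sequence its power is 90.9% at ρ = 0 and 97.6% at ρ = 0.3. If intervention is instead coded as the care received in each period, even an analysis that ignores pairing compares 36 with 36 observations and has 91.7% power at ρ = 0. On both readings the stated 90% is met.

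That stands as far as power goes. A reader might infer from the between-subjects label that the trial really has about 64% power and not 90%. The document does not support this. The 64.5% belongs to a single-period comparison of 18 infants with 18 others, which is planned nowhere; the model uses both T2 and T4. Nor is 36 an arithmetic error, since it follows from a standard crossover calculation.

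The reply does not remove the point. The article does more than stay silent on detail: it states a factor type that contradicts its design, and it writes out two contrasts from which the treatment effect is absent. Those contrasts make a mere slip in labelling a poor explanation.

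**Conclusion.** Wrong as written. Taken literally, neither main effect and neither listed contrast in Data analysis estimates intervention versus standard care. At a true difference of 0.04 the group main effect and the listed contrasts reject at about 5%. The cancellation is algebraic and does not depend on the SD or the correlation; it assumes only that the groups receive the two types of care in opposite orders and that there is no carryover. The 5% for the two contrasts further assumes no period effect. With one, they would detect change between weeks 2 and 4, not treatment.

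Among the readings tried, the stated 36 for 90% power reproduces only for a within-infant crossover analysis with an SD of 0.05 used as within-infant. The text calls that SD inter-person and derives it from a pilot of different infants, five against five. If 0.05 is the total SD and an infant's two measurements are positively correlated, the calculation is conservative. The fault is a mismatch between the stated model and the basis of the sample size. It is not a shortfall in recruitment.

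**What to change.** In **Data analysis**:

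- Define intervention as a within-infant, period-level factor: the type of care received in that period.
- Fit treatment, period and sequence as fixed effects, with a random infant effect.
- Make the within-infant treatment contrast the primary test, and delete the A(T2) vs B(T4) and A(T4) vs B(T2) comparisons. Correcting the label alone would leave these wrong.

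In **Sample size calculation**:

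- State that 36 infants in total, each with both periods, give 90% power under a 2×2 crossover calculation with 0.05 taken as the within-infant SD (SD of the paired difference 0.071).
- Say that the 0.05 comes from a between-infant pilot, and that using it this way is conservative if it is the total SD and the two measurements are positively correlated.

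The cost is rewording two paragraphs. No extra infants and no new data collection are needed. The change should be documented before outcome data are analysed by group.
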